**Methods:**

This is a multicenter, ambispective, observational, open-cohort study that is expected to enroll 554 patients with EGC. The study was launched in May 2018 and is scheduled to end in March 2022. All enrolled patients should meet the inclusion criteria. Case report forms and electronic data capture systems are used to obtain clinical data, which includes demographic information, results of perioperative blood- and auxiliary examinations, surgical information, results of postoperative pathology, and the outcomes of postoperative recovery and follow-up. Patients are followed up every 6 months after surgery for a minimum of 5 years. The primary endpoint is the rate of lymph node metastasis (LNM), whereas the secondary endpoints include the following: consistency, sensitivity, and specificity of the results of preoperative examinations and postoperative pathology; cut-off values for LNM; logistic regression model of expanded indications for ESD; and incidence of postoperative complications within the 30-day and 5-year relapse-free survival rates.

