### Secondary endpoints

Accuracy, specificity, and sensitivity are evaluated using the following gold standards: postoperative histopathology of ultrasonic gastroscopy for tumor invasion depth, abdominal and pelvic enhanced computed tomography (CT) scan for LNM, pathological biopsy for tumor differentiation, and auxiliary examination for TNM staging.Cut-off values for LNM: A receiver operating characteristic curve is drawn for the clinical characteristics under different LNM rates to obtain the cut-off values.Logistic regression model: To explore the corresponding logistic regression model, postoperative histopathological examination for LNM, depth of infiltration, and degree of differentiation are evaluated in the univariate analysis. Variables with statistical significance in the univariate analysis are examined in the multivariate analysis.Complications: The incidence of postoperative complications within the last 30 days, including anastomotic fistula, pancreatic fistula, intestinal obstruction, delayed bleeding, and incision-related complications, are recorded. Postoperative complications classified as higher than Grade II, according to the Clavien–Dindo classification are regarded as clinically significant (Tables 2), [16].Five-year relapse-free survival rate: The time interval from the date of operation to the detection of tumor recurrence within 5 years is recorded.

**Table 2 Tab2:** Clavien–Dindo classification

Grade	Definition
I	Any complication that deviates from the natural course of the operation; treatments include antiemetic, antipyretic, analgesic, and diuretic drugs; infusion; physical therapy; as well as bedside debridement of incision infection.
II	Medications other than those permitted for grade I complications are required, including blood transfusion and total parenteral nutrition support.
III	Surgical and endoscopic interventions and radiotherapy are required.
IIIa	No general anesthesia is required.
IIIb	General anesthesia is needed.
IV	Life-threatening complications requiring intensive care.
IVa	Single-organ dysfunction
IVb	Multi-organ dysfunction
V	Death

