#### Perioperative treatment for enrolled patients

For patients who underwent radical surgery, clinicians will provide symptom-based treatment, such as antibiotics, proton pump inhibitors, analgesics, octreotide, total parenteral nutrition support, and blood products, according to the patient’s recovery. Routine postoperative blood tests, biochemistry tests, blood amylase, and abdominal drainage fluid amylase will be reviewed regularly to monitor for anastomotic leakage, delayed bleeding, and pancreatic leakage. There will be a regular abdominal ultrasound examination to monitor for peritoneal effusion. If necessary, drainage by abdominal puncture will be performed. After return to a normal diet, patients with LNM or undifferentiated tumors will receive adjuvant chemotherapy 3–4 weeks after surgery.

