#### Data collection

A uniform case report form (CRF) was designed, and the electronic data capture (EDC) system was already established before the commencement of the clinical trial. All data are provided on the CRF. Subsequently, the clinical research coordinator (CRC) enters the data into the EDC system promptly (https://edc-cloud.medsci.cn/#/login). Every month, clinical research associates monitor the electronic database to ensure data quality.

The CRF includes the following data: 1) Demographic information: sex, age, length of hospital stay, body mass index, family disease history, concomitant disease, ECOG score, nutrition risk screening 2002 (NRS 2002) score, and venous thromboembolism score; 2) Perioperative laboratory tests: results of routine blood tests, biochemical investigations, and tumor marker evaluations, including CA19–9, CA125, AFP, CEA, and CA724; 3) Auxiliary examination: all the enrolled patients undergo an abdominal enhanced CT scan and low-dose plain CT scan of the chest, a positron emission tomography (PET)/CT examination when necessary, and an ultrasound gastroscopy or magnified gastroscopy; 4) Surgical information: ASA score, operation date, operation time, blood loss, surgical methods, degree of lymph node dissection, and intraoperative complications; 5) Postoperative pathology: the number of tumor lesions, tumor size, tumor location, surgical margin, gross type of tumor, histopathological type, Lauren type, depth of tumor invasion, number of lymph nodes dissected, and total number of LNM; and 6) Postoperative recovery outcomes: total hospitalization cost, postoperative complications and death, and recovery time of intestinal function (Table 3).

**Table 3 Tab3:** Checklist for the collection of necessary clinical data and follow-up scheme of enrolled patients with EGC

	Baseline information		Follow-up after operation													
	Preoperation	Operation	POD 1	POD 3	POD 7	POD 30	6 months	1 year	18 months	2 years	30 months	3 years	42 months	4 years	54 months	5 years
**Informed consent**	×															
**Demographic information**	×															
**Laboratory tests**	×		×	×	×	×	×	×	×	×	×	×	×	×	×	×
**Chest CT scan**	×							×		×		×		×		×
**Abdominal CT scan**	×						×	×	×	×	×	×	×	×	×	×
**Gastroscopy**	×							×		×		×		×		×
**Abdominal ultrasound**	×						×	×	×	×	×	×	×	×	×	×
**Physical examination**	×						×	×	×	×	×	×	×	×	×	×
**Surgical information**		×														
**Pathology**		×														

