#### Follow-up

The postoperative follow-up is performed by a dedicated investigator. The patients are followed up every 6 months after discharge using outpatient visits, telephone, or mail. During the follow-up period, the patients undergo physical examinations, laboratory tests, a gastroscopy, a chest and abdominal CT scan, or an abdominal ultrasound assessment. The laboratory tests include routine blood examination, blood biochemistry, and tumor marker evaluation that includes CA19–9, CA125, AFP, CEA, and CA724. For patients that develop postoperative tumor recurrence or distant metastasis, a further detailed evaluation, including abdominal magnetic resonance imaging or PET/CT, will be performed to determine the feasibility of surgical resection. Each patient will be followed for at least 5 years or until a loss to follow-up. The detailed follow-up schedule is shown in Table 3.

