### Statistical analysis

SPSS 21.0 (IBM Corp., Armonk, NY, USA) statistical software is used for the statistical analysis. The quantitative variables are described as the mean ± standard deviation and are tested by univariate analysis of variance for normal distribution; on the contrary, they are described as the median (interquartile range) and tested by the Kruskal-Wallis H test for non-normal distribution. The categorical variables are described as frequency (N) with the percentage (%) and tested by χ^2^ test, corrective χ^2^ test, or Fisher’s exact test. Ranked data are expressed as frequency and percentages and are compared using the Kruskal-Wallis H test. Sensitivity and specificity are calculated to evaluate the diagnostic performance. The Kaplan-Meier method is used to draw survival curves, and the survival of multiple groups are compared by the log-rank test. The univariate and multivariate Cox proportional hazards models are used to evaluate the hazard ratios for adverse outcomes. All statistical tests are two-sided, and a *P*-value < 0.05 is considered statistically significant.

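### The five-year relapse-free survival endpoint is defined by recurrence alone, so a death without recurrence would never lower the reported rate

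*Protocol article*

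**What the plan says.** The abstract names the endpoint without defining it: "incidence of postoperative complications within the 30-day and 5-year relapse-free survival rates". The definition is given once, in Secondary endpoints, under the label of a five-year relapse-free survival rate: "The time interval from the date of operation to the detection of tumor recurrence within 5 years is recorded".

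The Statistical analysis section gives the method for time-to-event outcomes: "The Kaplan-Meier method is used to draw survival curves, and the survival of multiple groups are compared by the log-rank test". It continues: "The univariate and multivariate Cox proportional hazards models are used to evaluate the hazard ratios for adverse outcomes". Neither sentence says what counts as an event or how a death is treated, and no competing-risk method is named.

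The Follow-up section says: "Each patient will be followed for at least 5 years or until a loss to follow-up". Death is not mentioned there. Death does appear in Data collection, among the postoperative recovery outcomes: "total hospitalization cost, postoperative complications and death, and recovery time of intestinal function". Table 3 schedules those outcomes on postoperative days 1, 3, 7 and 30 and at no later visit. Table 2 also lists death as Clavien–Dindo grade V.

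**The concern.** Relapse-free survival is ordinarily read as being alive and free of relapse, so both recurrence and death end it. The definition here keeps the name but drops half of the event. A death after surgery is the most severe complication in Table 2, yet the same death would not be a failure in an endpoint that has survival in its name.

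Two things are at stake. The reported five-year rate would be higher than relapse-free survival as readers understand it. It would also not be comparable with rates from series that count death as an event. Patients up to age 75 are eligible, so some deaths without recurrence over five years are to be expected.

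**Working it through.** **No figure to reproduce.** The article states no relapse-free survival rate, event count, target or power for this endpoint. The check is therefore a reading of the definition against the other sections, followed by an illustration of size.

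**Reading.** The definition in Secondary endpoints has one event, tumor recurrence. Four other places could have added death:
- The abstract only names the endpoint.
- Statistical analysis gives Kaplan-Meier, log-rank and Cox methods without an event definition; the Cox outcome is left as unspecified adverse outcomes.
- Follow-up ends at five years or at loss to follow-up.
- Data collection records death only as a recovery outcome and does not link it to relapse-free survival.

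None makes death an event.

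**Inputs for the illustration (assumed, not from the document).** Let *r* be the five-year net probability of recurrence, taken as 2% to 5%, and *d* the five-year net probability of death without recurrence, taken as 2% to 10%. The two are given independent constant hazards. The 3% in Determination of sample size is a lymph node metastasis rate; it is not the source of *r*.

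**Formulas.**
- Recurrence or death as the event: RFS = (1 − r)(1 − d)
- Recurrence only, deaths censored: KM = 1 − r
- Overstatement: KM − RFS = (1 − r) × d

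| r | d | KM, recurrence only | RFS, recurrence or death | Overstatement (points) |
|---|---|---|---|---|
| 2% | 2% | 98.00% | 96.04% | 1.96 |
| 2% | 5% | 98.00% | 93.10% | 4.90 |
| 2% | 10% | 98.00% | 88.20% | 9.80 |
| 3% | 2% | 97.00% | 95.06% | 1.94 |
| 3% | 5% | 97.00% | 92.15% | 4.85 |
| 3% | 10% | 97.00% | 87.30% | 9.70 |
| 5% | 2% | 95.00% | 93.10% | 1.90 |
| 5% | 5% | 95.00% | 90.25% | 4.75 |
| 5% | 10% | 95.00% | 85.50% | 9.50 |

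**Does the handling of deaths matter?** Suppose deaths were instead kept as relapse-free to five years. The reported rate is then 1 minus the cumulative incidence of recurrence, where

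CIF = [h_r / (h_r + h_d)] × (1 − RFS), with h_r = −ln(1 − r)/5 and h_d = −ln(1 − d)/5.

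For r = 3% this gives 97.0%, 97.1% and 97.2% at d = 2%, 5% and 10%, against 97.0% with deaths censored. Either way the rate exceeds RFS by about *d*. The choice between the two moves it by only about 0.2 points.

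**The case against.** The strongest reply is that an article condenses a fuller protocol, and that censoring rules normally sit in an analysis plan that is not shown. That holds for censoring: the article does not say how deaths are handled. A reader might infer that patients who die are counted as relapse-free to five years, but the text does not say so; under Kaplan-Meier, censoring at death is more likely. The reply does not cover the event itself, which is printed and does not fit its label.

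The size is also open to challenge. Entry requires ECOG and ASA scores of at most 2 and normal organ function, and it excludes cardiopulmonary insufficiency and other malignancy within five years. Deaths without recurrence may therefore be few. This stands: an overstatement of 5 to 10 points is the upper part of the assumed range, and nothing in the article supports saying that such deaths would outnumber recurrences.

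A reader might add that censoring deaths makes the recurrence probability itself invalid. The bias is real in principle, but at r = 3% it is about 0.2 points at most.

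A reader might also argue that log-rank comparisons are confounded because "patients with LNM or undifferentiated tumors will receive adjuvant chemotherapy". The article does not name the groups to be compared, plans multivariate Cox models as well, and bases the indications on lymph node metastasis rather than on survival. The objection would be to a use that the document does not describe. Nor would displaying survival from operation by chemotherapy actually received help: treatment starts 3–4 weeks after surgery, so early deaths fall into the untreated group by construction, which is immortal-time bias.

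**Conclusion.** The point holds as a mismatch between label and definition in one secondary endpoint. As printed, the endpoint is time to recurrence. Analysed by Kaplan-Meier and reported as relapse-free survival, it would be too high by roughly the proportion of patients who die without recurrence. The direction does not depend on whether deaths are censored or kept as relapse-free, because in neither case is a death a failure.

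The size cannot be taken from the document. It is about 2 to 10 points if 2% to 10% die without recurrence within five years, with recurrence at 2% to 5% and independent constant hazards, all of which are assumptions. The primary endpoint and the sample size, which both rest on the lymph node metastasis rate, are untouched. This should be corrected, but it does not threaten the study's main result.

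**What to change.** Define the event as the first of tumor recurrence or death from any cause, timed from the date of operation and censored at the last disease-free assessment. Report recurrence separately as a cumulative incidence with death as a competing event. If only recurrence is intended, rename the endpoint accordingly and drop the word survival.

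Record vital status and date of death at each existing 6-monthly contact. It should not be assumed that later deaths are already captured, since Table 3 covers death only within the recovery outcomes that end at postoperative day 30.

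The cost is one reworded definition, one added curve and one added follow-up item. That item may be incomplete in the retrospective cohort, recruited from January 2008 to April 2018, and its completeness should be reported there. The reported five-year rate will also be less favourable than under the present definition.

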### Inclusion criteria

Patients aged 18–75 years (regardless of sex).Patients with Eastern Cooperative Oncology Group (ECOG) score ≤ 2 points and American Society of Anesthesiologists (ASA) score ≤ 2 points who can undergo a radical D2 gastrectomy.Patients without a history of gastrointestinal operation, chemotherapy, or radiotherapy.Patients with normal liver, kidney, heart, lung, and bone marrow function (GPT × 10^9^/L, PLT>10^9^/L).Patients who can understand and comply with the research protocol.Patients who can provide written informed consent by themselves or through their legal agent.Gastroscopic and pathologic diagnoses based on the following criteria: ①Tumor diameter > 30 mm, ulceration (UL)(+), and differentiated, mucosal carcinoma (T1a); ②Tumor diameter > 30 mm and differentiated, submucosal invasion depth < 500 μm (T1b SM1); ③Tumor diameter ≤ 30 mm and differentiated, submucosal carcinoma (T1b); ④Tumor diameter ≤ 20 mm, UL(−), and undifferentiated (T1a); ⑤Tumor diameter > 20 mm, UL(−), and undifferentiated (T1a); ⑥Tumor diameter ≤ 30 mm, UL(+), and undifferentiated (T1a); ⑦Tumor diameter > 30 mm, UL(+), and undifferentiated (T1a). The detailed inclusion criteria are shown in Table 1.

**Table 1 Tab1:** Inclusion criteria of expanded indications for ESD in patients with EGC

	T1a				T1b			
	UL (−)		UL (+)		SM1		SM2	
	≤20 mm	> 20 mm	≤30 mm	> 30 mm	≤30 mm	> 30 mm	≤30 mm	> 30 mm
**Differentiated**	ESD	ESD	ESD	EXPANDED	EXPANDED	EXPANDED	EXPANDED	SURGERY
**Undifferentiated**	EXPANDED	EXPANDED	EXPANDED	EXPANDED	SURGERY	SURGERY	SURGERY	SURGERY

ESD, ESD absolute indication; EXPANDED, ESD expanded indication; SURGERY, surgical indication for EGC; EGC, early gastric cancer; ESD, endoscopic submucosal dissection

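### The Grade III row of Table 2 names radiotherapy and no grade names puncture drainage, so a drained patient can be graded on either side of the clinically significant threshold

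*Protocol article*

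**What the plan says.** The Secondary endpoints section of the protocol article makes the 30-day complication incidence a secondary endpoint. The complications are given as a list, "including anastomotic fistula, pancreatic fistula, intestinal obstruction, delayed bleeding, and incision-related complications, are recorded", with no grade attached to the recording. A second sentence sets the threshold: "Postoperative complications classified as higher than Grade II, according to the Clavien–Dindo classification are regarded as clinically significant". Table 2 in the same section supplies the grade definitions:

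- Grade I opens with "Any complication that deviates from the natural course of the operation" and then lists certain drugs, infusion, physical therapy and bedside wound debridement.
- Grade II reads "Medications other than those permitted for grade I complications are required, including blood transfusion and total parenteral nutrition support".
- Grade III reads "Surgical and endoscopic interventions and radiotherapy are required".
- Grade IIIa is the branch where "No general anesthesia is required"; IIIb is the branch where it is needed.

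The section on perioperative treatment describes monitoring for anastomotic leakage, delayed bleeding, pancreatic leakage and peritoneal effusion, and then says: "If necessary, drainage by abdominal puncture will be performed".

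**The concern.** The threshold sits between Grades II and III, so the Grade III row decides who is counted as having a clinically significant complication. That row has two faults. It includes radiotherapy, which does not belong among treatments for a fistula, an obstruction, a bleed or a wound problem. It also does not say where puncture drainage goes, although the protocol itself expects that procedure to be used.

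At stake is the consistency of one reported rate. Six hospitals contribute data, and 280 of the 554 planned patients (280 / 554 = 50.5%) are retrospective, so many grades may have to be assigned from existing records. Two careful graders using the same table could reach opposite answers for the same patient.

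**Working it through.** No figure in the article depends on this wording, so there is none to reproduce. The check sets the texts side by side.

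**1. Where the line falls.** Higher than Grade II means Grade III, IV or V. Grades IV and V concern life-threatening events and death. For a patient who is not critically ill, the Grade III row alone decides.

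**2. Does radiotherapy fit?** The perioperative treatment section gives it for no complication. Its only other appearance is in the inclusion criteria, as previous treatment: "Patients without a history of gastrointestinal operation, chemotherapy, or radiotherapy". Nothing in the article links it to the listed complications.

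**3. Is puncture drainage named in any row?**

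| Row of Table 2 | What it names | Puncture drainage named? |
|---|---|---|
| I | any deviation from the expected course; certain drugs, infusion, physical therapy, bedside wound debridement | no |
| II | other medication, transfusion, parenteral nutrition | no |
| III | surgery, endoscopy, radiotherapy | no |
| IIIa / IIIb | without / with general anaesthesia | no |

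**4. Which readings are open?**

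- *Below the threshold.* The opening of Grade I is wide enough to take any complication. Its list already includes a hands-on bedside procedure, and Grade III lists endoscopy separately from surgery, which suggests that surgical is not meant to cover every invasive act. A grader could leave a puncture in Grade I.
- *Above the threshold.* A puncture drain placed by the surgical team can be read as a surgical intervention without general anaesthesia, hence IIIa.

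**5. What moves.** Let N be the patients analysed, S those above Grade II for another reason, and D those whose highest treatment is puncture drainage. The clinically significant rate lies between S / N (all D graded low) and (S + D) / N (all D graded IIIa), a width of D / N. With N = 554, each such patient is worth 1 / 554 = 0.18 percentage points. The article gives neither S nor D, so the width cannot be worked out.

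**6. What does not move.** The listed complications are recorded whatever their grade, so their overall incidence stands. The lymph node metastasis rate and the sample size calculation do not use Table 2.

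**The case against.** The best defence is that the table is only an abridgement. The text grades according to a named classification with a citation, the section on the research supervision committee says each part of the trial has a standard operating procedure, and the surgeons are experienced. Graders who know the scale may never rely on the faulty row. The full protocol and the case report form guide are not shown, so divergence between centres is a possibility and has not been demonstrated. This limits the point to what may happen. It does not remove it: the text cites Table 2 and reference 16 together without saying which governs, and a mix of graders using one or the other would itself produce inconsistent grades.

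It is also fair to say that the perioperative section ties puncture most directly to peritoneal effusion, which is not among the named complications. That list is introduced as examples, however, and the same passage also covers monitoring for leakage and bleeding.

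A reader might infer more: that puncture drainage has no grade at all, or that drained patients drop out of the complication endpoint. The documents do not support this. Grade I can absorb such a patient, IIIa is an open reading, and the listed complications are recorded regardless of grade.

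**Conclusion.** The Grade III definition is faulty at the one boundary that matters for the clinically significant label, and it leaves the coding of puncture drainage undetermined. If such drainage is meant to count as Grade III, the error runs in one direction, towards too low a rate; if centres differ in their reading, part of any difference between them reflects wording. The effect is confined to the clinically significant subset of one secondary endpoint.

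The conclusion rests on Table 2 being used for grading, at least at some centres, and on puncture being the highest treatment for at least some patients. No percentage of missed events can be defended from the article. Nor can it be concluded that the result would fail to compare with other series using the scale, because the cited classification is not at hand. The matter is more than clerical, since the row is an operative outcome definition, but it should be corrected as a modest and inexpensive point.

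**What to change.** Change the outcome coding only; patient care is not touched.

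1. In the Grade III row of Table 2, replace radiotherapy with wording that covers non-surgical invasive procedures such as percutaneous drainage, and reconcile the row with the cited classification (reference 16).
2. State that therapeutic abdominal puncture drainage is coded as Grade III, with IIIa or IIIb decided by general anaesthesia as the table already does.
3. Put the same wording in the guidance for completing the case report form.
4. Recheck complications already entered, wherever the treatment given is recorded. The Data collection section lists complications but does not expressly list their treatment, so some entries may not be recoverable; report how many.

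The cost is a short text change and minor recoding. The reported rate of clinically significant complications may rise slightly.
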